### The SC treatment group

SC consists of 7 to 14 weekly, 60 min sessions of client-centered therapy. SC is based on the Traumagenic Dynamics Model of symptom formation after child sexual abuse and the Rogerian psychotherapy model. Supportive counselling sessions focus on establishing a trusting, empowering, and validating therapeutic relationship. Participants are allowed to choose when, how, and whether or not to address their trauma. In session 1, participants are oriented to SC.

Counsellors provide active listening, empathy, and encouragement to talk about feelings and express beliefs in the participant’s ability to cope. Participants direct the sessions. Counsellors note discussion of the trauma and the time devoted to such discussions. Tools such as problem solving and keeping a diary will be taught to participants.

Table 2 provides a detailed outline of the SC treatment program.

**Table 2 Tab2:** Outline of SC treatment, A detailed outline of the SC treatment

Major Focus	Goals	Sessions (ideal)	Present at session
Phase 1: Psychoeducation and treatment planning			
Module 1: Information gathering and Treatment Rationale	1. Build rapport 2. Gather information about the trauma 3. Give overview of treatment	1,2	Adolescent, Guardian (Full or partial)
Module 2: Treatment Planning Tool 1: Daily Diary	1. Gathering information about everyday problems 2. Give the rationale for supportive counseling 3. Introduce Daily Diary	2,3	Adolescent, Guardian (partial)
Phase 2: Treatment			
Module 3: Crisis Intervention and Coping Tool 2: Positive Problem Solving	1. Review Daily Diary 2. Provide Support 3. Practice Problem Solving	3–9 or 13	Adolescent
Phase 3: Relapse Prevention and Graduation			
Module 4: Generalization and Relapse Prevention	1. Review progress 2. Discuss the efficacy of various tools acquired in therapy. 3. Introduce generalization training and relapse prevention 4. Discuss the outcome of the therapy	10.11.12.13,or 14	Adolescent Parent (partial)
Module 5: Graduation	1. Review Progress with Parents/Guardians 2. Celebrate accomplishments 3. Reiterate Relapse Prevention Strategies	10,11,12,13, or 14	Adolescent, Guardian (partial)
Modules 1–5 Family intervention	1. Foster relationship with parent (s) 2. Inform the parents about the progress of treatment. 3. Address obstacles to treatment.	Throughout the treatment. Up to 3 additional sessions as needed to include parents with or without adolescent.	

### Measures

A pilot study of 12 participants [38] was used to determine the final assessment battery (from the included battery) that will be used for the study. The pilot study was also used to identify any logistical or treatment protocol implementation difficulties.

The assessment battery that will be administered to all adolescents who are eligible on screening is detailed below in Table 3.

**Table 3 Tab3:** Measures used in assessment, Measures used and indication when used in assessment

Domain	Measure	Assessing	Informant	Time (min)	Pre T1	Mid T2	Post T3	3, 6, 12 month FUs
Diagnostic Information	MINI-KID [45]	PTSD and other symptoms	*IE*	90	X			
	MRC Demographic Questionnaire	Demographic Information	*Parent*	10				
Psychopathology	CPSS [46, 47]	PTSD severity	*IE*	10	X	X	X	X
	CGAS [48]	*General Functioning*	*IE*	*5*	X	*X*	*X*	*X*
	BDI [49, 50]	*Depression*	*Adolescent*	*10*	X	*X*	*X*	*X*
	STAXI [51, 52]	*Anger*	*Adolescent*	*10*	X	*X*	*X*	*X*
	CBCL-YSR [53]	*General psychopathology*	*Adolescent*	*20*	X		*X*	*X*
	MASC [54, 55]	*Anxiety*	*Adolescent*	*5*	X	*X*	*X*	*X*
	PESQ [56]	*Substance use*	*Adolescent*	*15*	X	*X*	*X*	*X*
Cognition & Emotion	C-PTAS [57]	Trauma-related cognitions	*Adolescent*	10	X	X	X	X
	CAPS [58]	Attributions and perceptions	*Adolescent*	10	X	X	X	X
	PTCI [66]	Trauma-related cognitions	*Parent*	10	X		X	X
	NMR [59, 60]	Affect Regulation	*Adolescent*	10	X		X	X
	MSPSS [61, 62]	Social support	*Adolescent*	10	X	X	X	X
	Rosenberg [63]	Self-esteem	*Adolescent*	3	X	X	X	X
	CD-RISC [64]	Resilience	*Adolescent*	5	X	X	X	X
Symptoms – Parents	PDS [65]	PTSD	*Parent*	20	X		X	X
	BDI [49, 50]	Depression	*Parent*	10	X		X	X
Treatment variables	Expectancy-A	Tx expectancy	*Adolescent*	2	X			
	Satisfaction-A	Tx Satisfaction	*Adolescent*	2		X	X	X
	CPSS [41]	PTSD severity	*Adolescent*	10	Every session			
	Treatment compliance	Compliance with the treatment	*Therapist*	2		X	X	X

All measures will be obtained by an IE at baseline, mid-treatment (after 5 sessions), and post-treatment, and again at 3-month, 6-month and 12-month follow-up, and in following years at annual intervals, dependent on the availability of funds.

#### Diagnostic information

##### *The Medical Research Council Demographic Questionnaire* (MRCDQ)

The MRCDQ will be used to obtain each adolescent’s age, grade, gender and alcohol and drug use history from the adolescent, educator or parent. Information on the parents will include, age, educational level, marital status, income, employment, and their alcohol and drug use history.

##### *The Mini International Neuropsychiatric Interview for Children and Adolescents (MINI-KID;* [45]*)*

The MINI-KID is a semi-structured interview, administered by a trained clinical interviewer, covering current and lifetime disorders. It has excellent test-retest reliability (0.64–1.00).

#### Psychopathology measures

##### *The Child PTSD Symptom Scale–Interview (CPSS-I*; [46]*)*

The CPSS-I will be used in conjunction with the MINI-KID to assess PTSD diagnosis and PTSD symptom severity. The CPSS interview (8–18 years), is based on DSM-IV criteria and provide a Total-, re-experiencing-, avoidance- and hyperarousal score. The CPSS-I has 17 items that correspond with the DSM-IV and an additional 7 items. The CPSS-I Total score ranges from 0 to 51 and each item is rated from 0 to 3. Internal consistency ranged from .70–.89 for the total and symptom cluster scores. Test-retest reliability was good to excellent (.84 for the total severity score, .85 for re-experiencing, .63 for avoidance and .76 for arousal). Convergent validity was high (.80) between the CPSS and the Child Posttraumatic Stress Reaction Index [47]. A cutoff Total score of 11 or higher on the CPSS yielded 95% sensitivity and 96% specificity of diagnosis. The CPSS-I Total Score will be used as the primary outcome measure.

##### *The Child PTSD Symptom Scale – Self Report (CPSS-SR*; [46]*)*

The CPSS-SR is a self-report version with psychometric properties that are equivalent to the CPSS-I and will be utilized in every session as a repeated measure of PTSD symptoms and will also be part of the pre-treatment assessment package. It will be administered weekly as a self-report to monitor treatment progress and will be used to decide when to terminate treatment.

##### *The Children’s Global Assessment Scale (CGAS*; [48]*)*

The CGAS will be used by the IE to provide a measurement of general functional impairment and as a secondary outcome measure by the IE. It is an appropriate tool for children from age 4–18. The CGAS has demonstrated good inter-rater reliability (*r* = .85) when administered by trained clinicians.

##### *The Beck Depression Inventory (BDI;* [49, 50]*)*

The BDI, which has been normed for adolescents, will be used to assess depression. The BDI split half-reliability is .93, and correlations with clinician ratings of depression range from .62 to .65 [49]. The BDI will be used by the IE as a secondary outcome measure.

##### *The Spielberger State-Trait Anger Expression Inventory-2 (STAXI-2;* [51, 52]*)*: 1999)

The STAXI-2 is a 57 item self-report measure. It has a State-Anger subscale measuring the intensity of angry feelings and the extent to which a person feels like expressing anger at a particular time and the STAXI Trait-Anger scale that measures how often angry feelings are experienced over time, using a 4-point Likert scale. Anger control is measured by presenting descriptions of responses and participants rate how often they behave in the manner described when angry, also using a 4-point Likert scale. Norms are available for adolescents 16–19 years of age. Internal consistency (.88) is good. High scores on the STAXI-2 scales (75th percentile) indicate anger experience and expression that interferes with normal functioning. The STAXI-2 will be incorporated as a secondary measure.

##### *The Child Behavior Checklist-Youth Self Report (CBCL-YSR*; [53]*)*

A 112-item self-report screening tool for behavioural and emotional problems in children and adolescents. In this study, we report the Externalizing, Internalizing and Total Problem scores. Raw scores are converted to T-scores. On all three scales, a T-score of 70 and above is in the ‘Clinical’ range. A T-score of 65–69 is in the ‘Borderline Clinical’ range. It is normed for ages 11–18. The Total Problem Score has been shown to have excellent test-retest reliability (.87). The Total Problem Score, Internalising behaviour and Externalising behaviour scales will be used by the IE as secondary measures.

##### *The Multidimensional Anxiety Scale for Children (MASC*; [54, 55]*)*

The MASC is specifically designed to assess a wide spectrum of common anxiety symptoms in youth. The items are distributed across 4 major factors; physical symptoms, social anxiety, harm avoidance and separation anxiety the ratings are done on a 4-point Likert rating scale. The scale has been shown to be invariant across gender and age and shows excellent internal consistency and test-retest reliability [53]. A study showed that the same 4-factor structure applies to adolescents in the Cape Town metropole, when compared to North American and Icelandic samples [55]. Another important finding was that the 4-factor structure applied equally well to males and females, making between group comparisons possible within this context. The MASC also measures separate dimensions of anxiety amongst various racial groups, which makes it suited to discriminate patterns of anxiety in subgroups of youth with anxiety disorders.

##### *The Personal Experience Screening Questionnaire (PESQ*; [56]*)*

This measure was developed as a screening tool for drug use in adolescents. This scale provides a global measure of problem severity, by indicating to what extent adolescents are psychologically and behaviourally involved with drugs. The score on the problem severity scale varies from 0 to 54, with a score of 30 indicating a problematic level of drug use. Internal consistency ranges from .90 to .95 across normal, delinquent and substance-abusing adolescents. The PESQ Problem Severity score will be used as a secondary measure by the IE.

#### Cognition and emotion measures

Three measures of dysfunctional cognitions related to trauma will be administered to investigate the role of cognition in mechanisms of change:

##### *The Child Post-Trauma Attitudes Scale (C-PTAS*; [57]

This is a 30-item self-report measure for children 8 and older and generates a total score and 3 subscale scores for negative post-traumatic cognitions. The subscales measure perceptions about the dangerousness of the world, a sense of own competence, and isolation. The measure also yields a total score which ranges from 0 to 120. Internal consistency was moderate to high, with alphas ranging from .66 to .82 for the total C-PTCAS score and three subscales. The C-PTAS will be used as a secondary measure by the IE.

##### *The Children’s Attributions and Perceptions Scale (CAPS;* [58]

The CAPS is an 18-item scale that has been normed as an interview but will be used as a self-report measure. The CAPS rated on a 5-point Likert Scale has four subscales: Feeling Different from Peers, Personal Attributions for Negative Events, Perceived Credibility, and Interpersonal Trust. Internal consistency for the subscales ranges from .63 to .73. Test-retest reliability ranges from .60 to .82 for the subscales and is .75 for the total scale.

##### *The Negative Mood Regulation questionnaire (NMR;* [59]*)*

This is a 30-item measure of beliefs that individuals have, which, when they are in a bad mood, can effect a change to help them feel better. Higher scores indicate better expectancies around the ability to control negative mood. Test-retest reliability for the NMR was acceptable (.67–.78). Although this measure was not designed specifically to be used in adolescents, it has been used successfully in studies of depressed suicidal and non-suicidal adolescents [60]. The NMR will be used as a secondary measure by the IE.

Additionally, the following three adolescent self-report measures will be administered:

##### *The Multidimensional Scale of Perceived Social Support (MSPSS*; [61, 62]

The MSPSS is a 12-item self-report inventory that measures the perceived adequacy of social support from 3 sources; family, friends and significant other. The ratings are made on a 7-point Likert-Scale. The psychometric qualities of the MSPSS were evaluated within a South African context with the internal reliability of the scale and subscales found to be high (Cronbach alpha coefficients > 0.85) [62]. The MSPSSis psychometrically sound and has excellent internal validity in South African youth.

##### *The Rosenberg Self-Esteem Scale* [63]

This is a 10-item self-rating scale to assess self-esteem. The ratings are done on a 4-point Likert scale. The scale has been evaluated across multiple cultural contexts [63], including Western, Eastern and African contexts.

##### *The Connor-Davidson Resilience Scale (CD-RISC*; [64]

The CD-RISC is a 25-item self-report measure to assess resilience. Ratings are done on a 5-point Likert Scale.

#### Parental symptoms - moderators

Parental distress will be assessed as moderators of outcome. If parents themselves suffer from PTSD following a trauma, they might interfere with the exposure procedures.

##### *The Posttraumatic Diagnostic Scale (PDS*; [65]

The PDS will be used to measure the total and subscale severity scores and categorical classification of PTSD.

##### *The Beck Depression Inventory (BDI;* [49, 50]

The BDI will assess depression as it can be widely used in a variety of populations, including trauma victims [67] and the.

##### *The Post-Traumatic Cognitions Inventory (PTCI*; [66]

The PTCI is a 36-item self-report instrument that assesses dysfunctional post-trauma cognitions. Items are rated on a 7-point Likert Scale; this will be completed by the parent/guardian.

### Treatment related variables - mediators

Three self-report measures will be administered to examine their mediating effects on treatment outcome:*Expected Treatment Outcome (ETO)* will be provided by the adolescent on a 5-point Likert scale from “I expect this treatment to help me a lot” (5) to “I don’t expect this treatment to make any difference in my condition” (1).*Treatment satisfaction (WIAC)* will be provided by the adolescent on a 5-point Likert scale from “I am extremely satisfied with this treatment, it helped me a great deal” (5) to “I am not at all satisfied with this treatment, it did not help my condition” (1).*Treatment Compliance* will be assessed by the counsellor by ranking the adolescent’s compliance with treatment and homework on a 5-point Likert scale.

#### Qualitative study

Topic guides and interview schedules for the different qualitative groups are included in (Additional file 1: Table S4 – Table S6c). The Standard Operating Procedures (SOP) for adolescents, the initial telephone contact procedure with the adolescent’s parent, and the interview schedule and focus group topic guides to be used in the qualitative interviews can be found in (Additional file 1: Table S4, S4a and S4b). The SOP outline for the nurse counsellors, the initial telephone contact, the focus group topic guide and a questionnaire to be completed can be found in (Additional file 1: Table S5, S5a, S5b and S5c). The details of the SOP for teachers, the initial telephone contact and the focus group topic guide can be found in (Additional file 1: Table S6, S6a and S6b). The SOP for data coding and thematic analysis are presented in (Additional file 1: Table S7) and the details of the SOP for transport arrangements of participants to the Stellenbosch University Medical Campus are presented in (Additional file 1: Table S8).

### Data management and monitoring

Acquired data will be entered immediately into a database constructed using SPSS. Each entry form will be restricted to the possible range of items. Data entry and verification will be conducted independently by study assistants.

### Statistical analysis

#### Preliminary data analysis

Demographic characteristics and outcome measures at pre-treatment assessment will be examined using t-tests (for continuous variables) or chi-square tests (for nominal variables). These comparisons will enable the identification of control variables for use in later analysis for comparing treatment differences. The focus will be on both statistical and clinical significance of group differences (means and proportions of variants explained).

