#### General considerations for data analysis

Descriptive statistics will be gathered in order to determine if variables have a normal distribution and variables that violate assumptions of normality will be transformed. If this does not improve the normality of distribution, distribution free statistics will be used.

The study has pre-, mid-, post-treatment, three follow-up assessments and annual follow-up thereafter. This creates clustered data due to repeated measures. To examine treatment difference, generalized estimating equations (GEE) and a linear mixed-effects model approach (LMM) will be employed. Both approaches accommodate missing data. LMM will be the main analytical tool, particularly for estimating between-participant variability; GEE will be used to assess the robustness of the population parameters, such as treatment effects.

Analyses correlating the change in PTSD symptoms with each of the distress-related cognition and emotion variables at post-treatment will be performed, by pooling data across treatment conditions. Product-moment and Spearman’s rho correlation coefficients will be used.

Correlation analyses correlating the change in PTSD symptoms with each of the distress- related cognition and emotion variables at post-treatment, by pooling data across treatment conditions, will be performed. Product-moment and Spearman’s rho correlation coefficients will be used.

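### Between-arm significance tests at baseline choose the covariates for the treatment comparison, and the scope of the normality rule over the primary analysis is left open

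*Protocol article*

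**What the plan says.** The protocol article, under Preliminary data analysis, states that demographic characteristics and pre-treatment outcome measures "will be examined using t-tests (for continuous variables) or chi-square tests (for nominal variables"). It then gives the purpose: "These comparisons will enable the identification of control variables for use in later analysis for comparing treatment differences". On how a variable qualifies, it says only: "The focus will be on both statistical and clinical significance of group differences". It gives no threshold and no fixed list.

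Under General considerations for data analysis it adds a distributional rule: "variables that violate assumptions of normality will be transformed", and then "If this does not improve the normality of distribution, distribution free statistics will be used". The same section names the treatment-effect methods, a linear mixed-effects model (LMM) and generalized estimating equations: "LMM will be the main analytical tool, particularly for estimating between-participant variability". It describes the repeated structure thus: "The study has pre-, mid-, post-treatment, three follow-up assessments and annual follow-up thereafter". The section on the interview scale says: "The CPSS-I Total Score will be used as the primary outcome measure".

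**The concern.** Covariate adjustment in a randomised trial earns its precision from prognosis: a covariate helps because it predicts the outcome, whether or not the arms differ on it. A between-arm test at baseline measures something else. With 1:1 randomisation, any difference it finds is chance. A strong predictor is therefore left out in most realisations of the trial, and a weak one may enter by accident. Because clinical significance is also weighed without a stated limit, the covariate set can be settled only after the baseline data by arm have been seen.

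This is a rule that the article states. It is not a detail left for an analysis plan to supply, and an analysis plan that follows the article would inherit it.

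The distributional rule raises a second, smaller point. It is applied to variables, whereas the LMM's assumptions concern residuals and random effects, and it does not exempt the primary outcome. If it were applied to the CPSS-I, a transformed or rank result would no longer estimate a difference in CPSS-I points. A simple rank test would also give up the handling of missing data for which the article chose its models, in a trial that expects up to 30% dropout.

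**Working it through.** **Design inputs.** From the Sample size section: 64 completers, 80% power, two-tailed alpha 0.1, 30% dropout, 90 entrants. From the Design section: 1:1 allocation, hence 32 completers per arm.

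**The plan's own figures.** The dropout step is reproduced to within 2: 64 / 0.7 = 91.4, i.e. 92 entrants, and 90 × 0.7 = 63 completers. The 64 itself cannot be reproduced, because no numerical effect size or SD is given. Solving backwards, d = (1.645 + 0.842) × √(2/32) = 0.62. This d is an assumption used below, not a figure from the article.

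**Covariate rule: simulation.** One post-treatment score, one covariate with correlation r to the outcome (0.3, 0.5 and 0.7 assumed), 32 per arm, two-sided alpha 0.10, 20,000 trials per setting. Under the test-selected rule the covariate enters only if its baseline t-test gives p<0.05 (assumed, as the article sets no threshold).

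| r | Power, unadjusted | Power, test-selected | Power, prespecified | Loss from selection | Type I error, test-selected |
|---|---|---|---|---|---|
| 0.3 | 0.790 | 0.791 | 0.815 | 0.024 | 0.096 |
| 0.5 | 0.792 | 0.801 | 0.878 | 0.077 | 0.090 |
| 0.7 | 0.795 | 0.813 | 0.962 | 0.149 | 0.082 |

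The covariate entered in about 5% of trials, so the test-selected analysis is close to no adjustment. The Monte Carlo standard error of a 0.10 rate is √(0.1 × 0.9 / 20,000) = 0.002. The fall in type I error is therefore clear at r = 0.5 and 0.7 and marginal at 0.3. It lies in the conservative direction.

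**How much the LMM may already recover.** The pre-treatment score is one of the model's time points, so baseline information is not simply absent. What is recovered depends on the contrast. Relative to a post-only difference, the variance is 1 for post only, 2(1 − r) for change from baseline and 1 − r² with baseline adjustment. Power is Φ(0.622 × √(32/2) / √(relative variance) − 1.645), where 0.622 × 4 = 2.49:

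| r | Post only | Change | Baseline-adjusted |
|---|---|---|---|
| 0.4 | 80% | 73% | 86% |
| 0.5 | 80% | 80% | 89% |
| 0.6 | 80% | 87% | 93% |

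At r = 0.5 a plain change contrast recovers nothing, since 2(1 − 0.5) = 1, and at 0.4 it does worse than the post-only comparison. At 0.6 it recovers about half of the gain. A common baseline mean in the LMM comes close to the adjusted column. The article does not say which form is meant.

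**Distributional rule.** In a parallel simulation (8,000 trials, r of 0.3 to 0.7), a Shapiro-Wilk test at p<0.05 switched from ANCOVA to Mann-Whitney, with no transformation step.
- Normal data: the switch occurred about 5% of the time and power fell by 0.3 to 1.1 points (0.814 to 0.811, 0.875 to 0.869, 0.959 to 0.948).
- Strongly skewed lognormal data with a pure shift: the rank route gained power (0.985 to 0.987 against 0.825 to 0.913 for ANCOVA).
- A floor-type gamma distribution went the other way (Mann-Whitney 73% against t-test 81%).

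The direction depends on the assumed shape, so no general power effect can be stated.

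**The case against.** The strongest objection on covariates is that the simulation is not the planned analysis. It compares a t-test with ANCOVA at one time point, while the plan uses an LMM that includes the pre-treatment score. That stands, and it makes the losses upper-range figures. It holds for secondary outcomes as well as for the CPSS-I, because Table 3 lists pre-treatment scores for functioning, depression, anger, general psychopathology and anxiety too. It does not remove the point, since recovery depends on a parameterisation that the article leaves open, and a covariate other than the outcome's own baseline gains nothing from that time point.

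It is also fair to say that power under the test-selected rule stays at about 79% to 81%, the level for which the trial was sized. The loss is measured against what the same data could give, not against the stated target. A reader who inferred that the rule inflates false positives would be mistaken: it makes the test conservative.

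On the distributional rule, a reader might infer that a failed normality check replaces the LMM. The article does not say so. It keeps the LMM as its principal method, and the rule, placed among general considerations, may be meant for the simpler analyses, such as the correlations for which both product-moment and Spearman coefficients are planned. A reader might also infer that stopping treatment at 70% improvement forces the primary outcome towards zero. But that rule uses the self-report CPSS-SR, not the evaluator-rated CPSS-I, and treatment is capped at 14 sessions whether or not the improvement is reached. Skewed CPSS-I scores are plausible; the documents do not establish them.

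**Conclusion.** The point on covariate selection holds. The article lets tests of chance imbalance decide what the treatment comparison is adjusted for. The cost is about 2 to 15 points of power against prespecified adjustment for correlations of 0.3 to 0.7, with type I error of about 8% to 10% at a nominal 10%. These figures rest on d of 0.62, the assumed correlations, an assumed p<0.05 gate and a single time point. For an outcome with its own pre-treatment score they are an upper range.

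The point on the distributional rule is narrower. The rule is framed on variables, does not exempt the primary outcome, and is not reconciled with the LMM. What is at stake is the estimand and, with a simple rank test, the handling of missing data. The documents support neither a general loss of power in that branch nor the statement that the LMM is abandoned.

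**What to change.** 1. Delete the baseline tests as a selection rule and report baseline characteristics descriptively by arm.
2. Prespecify, for the CPSS-I and each secondary outcome, the baseline value of the same measure as a covariate, or fit the LMM with a baseline mean constrained to be common to both arms. Fix any further prognostic covariates before unblinding. The documents do not show which others are prognostic, so that choice belongs to the trial team.
3. State that the primary CPSS-I analysis stays the LMM on the original scale, with checks on the residuals and robust or bootstrap confidence intervals if these are poor. Make transformed and rank analyses sensitivity analyses only, and say to which other analyses the distributional rule applies.

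The cost is a change of wording, about one degree of freedom per model and minor extra analysis work. The pre-treatment scores are already in the assessment schedule.
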